	**Study period**						
	**Screening**	**Enrolment and randomisation**	**Surgery**	**Post-surgery**			
Time point (weeks)	0	2	6 to 12	2	6	12	56
Enrolment:							
Eligibility screen	X						
Informed consent		X					
Randomisation		X					
Intervention:							
Arthrodesis			X				
Hemiarthroplasty			X				
Assessment:							
Patient demographics		X					
MOXFQ		X			X	X	X
AOFAS-Hallux		X			X	X	X
EQ-5D-5 L		X			X	X	X
Clinical review				X	X		X
Radiological review					X		X

At the 12-month follow-up, patients will additionally have a short structured interview with the research nurse to ascertain the acceptability of the trial process as a whole, the acceptability of the randomisation process and any aspects that could be improved. The operating surgeons (both senior authors) will also undergo similar structured interviews at the conclusion of the trial. This qualitative data will be collated and used to determine what areas of the trial design and conduct need to be addressed before embarking on a larger prospective multi-centre randomised control trial.

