## Methods/Design

This study will run as a prospective single-centre randomised controlled trial with two parallel treatment arms containing 15 participants each and comparing PPH with arthrodesis (the current gold standard for the treatment for hallux rigidus). The primary objective is to determine the range of improvement in outcome scores following these procedures. The secondary objective is to determine the patient recruitment rate, trial dropout rate (including those lost to follow-up) and the acceptability of the trial as a process to surgeons and patients (by way of qualitative interviews). The combination of the primary and secondary objectives will be used in a power calculation and to design a larger, multi-centre randomised, controlled trial with longer follow-up.

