### Patient recruitment

Patients will be screened and recruited by three consultant foot and ankle orthopaedic surgeons from outpatient clinics (in the East Lancashire Hospitals NHS Trust) after confirmation of diagnosis and eligibility (see Table 1). Screening will continue until the target sample size is reached (15 patients in each arm). The number of patients to be recruited has been based on discussions with the trial statistician. There is no published data using the MOXFQ tool to assess differences between PPH and arthrodesis. Therefore, a power calculation was not performed.

**Table 1 T1:** Eligibility criteria

**Inclusion**	**Exclusion**
1. Coughlin grade 3 to 4 hallux rigidus with near constant pain and stiffness at least at extremes of passive motion +/− mid range of motion pain, where conservative treatment measures have failed	Inflammatory arthritis
	Active infection
	Severe vascular or neurological deficit affecting the lower limbs
	Hallux valgus angle >15°
	Inadequate or poor quality bone stock
2. Aged 45 years or above	Any previous surgery to the first MTPJ other than a cheilectomy
3. Male or female	
4. Able to give informed consent	
	Significant and symptomatic interphalangeal joint or sesamoid-metatarsal osteoarthritis

Patients who meet the eligibility criteria will be provided with a patient information sheet and given 1 to 2 weeks to go over this information. If agreeable, informed consent for entry into the trial will be obtained from patients before randomisation is performed. Randomisation will be performed using a random computer generated sequence with a 1:1 allocation ratio in blocks of six. The online website Sealed Envelope [22] has been used to do this. Allocation concealment will be ensured by using a locked spreadsheet, which will only reveal the allocated treatment arm after a patient’s hospital number and study number have been entered. Given the nature of surgical procedures, the only person involved in this trial who will remain blinded to treatment arm allocation is the statistician. Surgeons and patients cannot be blinded to the treatment arm. The outcome measures used in this study are all patient administered and therefore this study does not require a blinded assessor.

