### Interventions

Surgery will be performed by one of the three consultant orthopaedic foot and ankle surgeons who are FRCS (Trauma & Orthopaedics) qualified and on the General Medical Council’s Specialist Register.

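### Patients are interviewed on acceptability only at 12 months, so those who leave after allocation are not heard; the count of operating surgeons (two or three) also needs reconciling

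*Protocol article*

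**What the plan says.** The Methods/Design section of the protocol article lists among the secondary objectives "the acceptability of the trial as a process to surgeons and patients (by way of qualitative interviews", alongside recruitment and dropout rates.

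The text after Table 2 (Data collection) says how this is done. For patients: "At the 12-month follow-up, patients will additionally have a short structured interview with the research nurse to ascertain the acceptability of the trial process". The same interview is to cover "the acceptability of the randomisation process and any aspects that could be improved". For surgeons: "The operating surgeons (both senior authors) will also undergo similar structured interviews at the conclusion of the trial". The collated material is to show what must change before a larger multi-centre trial.

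Two other sections bear on the surgeon sentence. Patient recruitment: "Patients will be screened and recruited by three consultant foot and ankle orthopaedic surgeons from outpatient clinics". Interventions: "Surgery will be performed by one of the three consultant orthopaedic foot and ankle surgeons".

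Table 2 puts randomisation at week 2, surgery at weeks 6 to 12, and post-surgery contacts at weeks 2, 6, 12 and 56. It has no row for an interview at any earlier time. Under Statistical methods, dropout rates are to be reported at each time point.

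**The concern.** In a 30-patient study without a power calculation ("Therefore, a power calculation was not performed"), feasibility information is a main product. An interview tied to the final visit reaches only people who accepted their allocation and stayed. A patient who leaves because of the allocation, or because the trial was burdensome, could best say what needs changing, and the plan as described does not reach that patient.

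Timing is a second problem. A question about randomisation asked after the operation has succeeded or failed is partly a question about the operation.

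For surgeons, the text leaves unclear whether everyone who recruits and operates will be asked. What is at stake is the next trial: if the reasons for leaving are not collected, it may repeat the features that caused people to leave.

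**Working it through.** The plan gives no acceptability figure to reproduce. The check is of timing and of consistency between sections.

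**1. Who can be missed, and when.** By Table 2, surgery follows randomisation by 6 − 2 = 4 to 12 − 2 = 10 weeks. Patients are not blinded (Patient recruitment), so someone unhappy with the allocation may leave in that interval, before surgery. Others may be lost between surgery and the last visit. No interview is described for either group.

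**2. How late the randomisation questions come.**
- Last visit at post-surgery week 56, as in Table 2: 4 + 56 = 60 to 10 + 56 = 66 weeks after randomisation.
- If 12 months is taken as 52 weeks after surgery: 4 + 52 = 56 to 10 + 52 = 62 weeks.

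On either reading the gap exceeds a year. At the existing 6-week visit it would be 4 + 6 = 10 to 10 + 6 = 16 weeks.

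**3. Whether other planned data fill the gap.** Recruitment and dropout rates will be reported. They show how many patients left and at which time point, but not why.

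**4. Possible size, as an illustration only.** Suppose acceptability were summarised as a proportion, which the plan does not say it will be. With dropout *d* and proportions *p_c* among completers and *p_d* among dropouts who find the trial acceptable,

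overstatement = *p_c* − [(1 − *d*)·*p_c* + *d*·*p_d*] = *d*·(*p_c* − *p_d*).

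All inputs are assumptions. With *p_c* = 90%:

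| Dropout | *p_d* = 90% | *p_d* = 50% | *p_d* = 30% |
|---|---|---|---|
| 5% | 0 points | 2 | 3 |
| 10% | 0 | 4 | 6 |
| 20% | 0 | 8 | 12 |
| 30% | 0 | 12 | 18 |

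For example, 0.10 × (0.90 − 0.50) = 0.04. The range is 0 to 18 points. The sign would reverse if dropouts were more accepting than completers.

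**5. Surgeons.** Patient recruitment gives three recruiting consultants and Interventions gives three operating consultants. The interview sentence identifies the operating surgeons with the senior authors by the word *both*, which means two. Either one surgeon is not interviewed, or the count of three is wrong, or *both* is a slip. The article does not allow a choice between these.

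**The case against.** The strongest counter-argument is that the interviews are qualitative. They are to be collated to find problems, with no percentage, threshold or progression rule, so a biased proportion is not something the plan would report. This stands. The table above only shows that the effect could be nil or substantial, and the durable point is the missing reasons.

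Second, a reader might infer that the results will be biased towards acceptance. The document does not show this. Dropout may have nothing to do with acceptability, and knowing the surgical result can push opinion either way: a patient with non-union or re-operation may judge the trial more harshly. Overstatement is the expected direction, no more.

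Third, a reader might infer that one of three surgeons is excluded. The sentence covers the operating surgeons without limit, and *both* sits in a parenthesis. This is a contradiction, not proof of exclusion. The authorship of those interviewed is stated, but adding a third surgeon, who also takes part in the trial, would not remove that interest.

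Fourth, this is an article condensing a fuller protocol, which may record reasons for withdrawal or for declining. That disposes of any complaint about the screening log or about patients who decline. It does not dispose of the interview point, because the article itself states who is interviewed and when.

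Finally, the process as a whole can only be judged at the end, so 12 months is right for those questions. This stands too.

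**Conclusion.** The concern holds in a limited form. As described, the patient interviews leave out anyone who withdraws or is lost between allocation and 12 months, and collect views on randomisation 56 to 66 weeks after it, once the surgical result is known. They may therefore miss the reasons for dropout and may present the trial as more acceptable than it was. Neither the size nor the direction can be derived from the article, which gives no dropout rate, no acceptability rate and no planned numerical summary.

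The conclusion rests on the article describing the interviews completely. If the full protocol also provides for interviews at withdrawal, the selection part falls away and the timing of the randomisation questions remains. The two-versus-three surgeon conflict is an inconsistency to be reconciled and supports nothing further. Overall this is a worthwhile, inexpensive improvement to a secondary objective; it does not touch the MOXFQ comparison.

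**What to change.** - Ask the questions on acceptability of randomisation at the existing 6-week clinical review.
- Offer the same short interview, optional and by phone, to anyone who withdraws. This is needed as well as the 6-week visit, because a patient who leaves before surgery does not reach that visit.
- Keep the questions on the trial process as a whole at 12 months.
- Reconcile the surgeon count across Patient recruitment, Interventions and the text after Table 2, and state that all surgeons who recruit or operate are interviewed.

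The cost is a few short extra contacts by the research nurse already in the plan, and a minor amendment. No outcome assessment changes. The remedy is partial: recall is shortened to about 10 to 16 weeks and not removed, and some patients who withdraw or are lost will still not answer. Recruitment is under way, so patients already past the 6-week visit can only be asked later.

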### Statistical methods

The primary analysis will compare MOXFQ scores between the two treatment groups at 12 months using a *t*-test, adjusting for the score at baseline. A similar analysis will be carried out to investigate differences in secondary outcomes (AOFAS-Hallux and EQ-5D-5 L) between the two treatment groups. Effect sizes will be presented as a point estimate, 95% confidence intervals and *P* values. Rates of patient dropout will be reported at each time point. The observed effect size will be used in a power calculation for a future definitive trial.

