**Methods/Design:**

The primary objectives are to determine the range of outcome scores between the two treatment arms (to inform a power calculation). Outcome measures will include the MOXFQ, AOFAS-Hallux and EuroQol EQ-5D-5 L. Secondary objectives are to determine the accrual rate, dropout rate and trial acceptability to both patients and surgeons. These data will allow the development of a larger trial with longer follow-up.

This is a prospective randomised controlled single-centre study comparing proximal phalanx hemiarthroplasty (AnaToemic, Arthrex Ltd., Sheffield, UK) with arthrodesis (15 patients in each arm). Randomisation will be performed using a 1:1 allocation ratio in blocks of six.

Patients meeting the eligibility criteria will be recruited from three foot and ankle consultant surgeon’s clinics (East Lancashire Hospitals NHS Trust). If agreeable, informed consent will be obtained before patients are randomised.

The outcome measure scores will be completed pre-operatively and repeated at 6 weeks, 3 months and 12 months. A radiological review will be performed at 6 weeks and 12 months to determine rates of loosening (hemiarthroplasty) and union (arthrodesis). Data on length of stay, return to work, complications and re-operation rates will also be collected.

The analysis will compare the change in outcome scores between treatment groups at all follow-up time points. Scores will be compared using a Student *t*-test, adjusting for scores at baseline.

This study will be conducted in accordance with the current revision of the Declaration of Helsinki (1996) and the ICH-GCP Guideline (International Conference on Harmonisation, Good Clinical Practice, E6(R1), 1996). This study has been approved by the sponsor, the Trust Research & Development office. Ethical approval has been received from the National Research Ethics Service (North East: 12/NE/0385 for protocol version 5.3 dated 3 June 2013).

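### The primary analysis gives the 6-week and 3-month MOXFQ scores no role, so a patient lost after 3 months contributes nothing unless the 12-month score is imputed; this can bias the 12-month difference

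*Protocol article*

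**What the plan says.** The Statistical methods section fixes the primary analysis: "The primary analysis will compare MOXFQ scores between the two treatment groups at 12 months", using a t-test and "adjusting for the score at baseline". A similar analysis is planned for AOFAS-Hallux and EQ-5D-5L. On missing follow-up the section says only: "Rates of patient dropout will be reported at each time point".

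The abstract describes the data: "The outcome measure scores will be completed pre-operatively and repeated at 6 weeks, 3 months and 12 months". Table 2 agrees, with MOXFQ marked at enrolment and in the 6-week, 12-week and final columns. The abstract words the analysis differently: "The analysis will compare the change in outcome scores between treatment groups at all follow-up time points", again by a t-test with baseline adjustment and no model that joins the time points.

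The design has "two parallel treatment arms containing 15 participants each". On sample size, Patient recruitment says: "Therefore, a power calculation was not performed". The result will be reused: "The observed effect size will be used in a power calculation for a future definitive trial".

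**The concern.** The named method uses two scores per patient, baseline and 12 months. A patient who completes 6 weeks and 3 months and is then lost has two informative follow-up scores on file, and neither enters the primary comparison. Leaving that patient out is harmless if loss is unrelated to how the toe is doing, given arm and baseline. It can do harm if patients with poor early results leave more often.

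Selective loss is plausible here. Patients and surgeons know the treatment. Table 2 schedules no MOXFQ and no clinical review between the 12-week and the final column. The failure rates cited in the Background differ by procedure: 24% re-operation for hemiarthroplasty in one retrospective series, against up to 10% non-union for arthrodesis. At stake is the 12-month difference, which is meant to feed the sample size of the definitive trial.

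**Working it through.** **1. What enters the comparison.** The stated analysis amounts to Y12 = a + b·arm + c·Y0 + error, where Y0 and Y12 are the baseline and 12-month scores. A patient without Y12 supplies no equation, and the 6-week and 3-month scores appear nowhere. With complete data, a repeated-measures model with unstructured covariance, arm-by-visit and baseline-by-visit terms gives the same 12-month point estimate, because every visit has the same regressors. The two methods therefore part only over patients who lack some follow-up scores.

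**2. No figure to reproduce.** The article gives no effect size, SD, power or dropout rate. For scale, 15 per arm at two-sided 5% has 28% power for a difference of 0.5 SD and 80% for about 1.02 SD.

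**3. Simulation.** From the article: 15 per arm, the visits, baseline adjustment. Assumed: SD 1; correlation of baseline with each visit 0.4; 6 weeks with 3 months 0.6; 6 weeks with 12 months 0.5; 3 with 12 months (r) 0.5 or 0.7; target loss after 3 months 10% or 20%; 6,000 trials per scenario. Higher scores are worse. Under selective loss, 80% of patients beyond a cut-off in the worst tail leave. In the one-arm scenarios, the other arm loses patients at random at the target rate.

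Two estimators were compared: the baseline-adjusted comparison of 12-month completers, and a likelihood-type estimator. The latter regresses Y12 on arm, baseline, 6-week and 3-month scores in completers, predicts for everyone, then adjusts for baseline. Negative bias makes the arm losing more of its poor scorers look better than it is.

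| Loss after 3 months | True effect | Bias, completers (SD) | Bias, all visits (SD) |
|---|---|---|---|
| Random | 0 | 0.00 | 0.00 |
| Poor 3-month scorers, same rule in both arms | 0 | 0.00 | 0.00 |
| Poor 3-month scorers, same rule in both arms | 0.5 SD | −0.05 to −0.10 | 0.00 |
| Poor 3-month scorers, one arm only | 0 | −0.06 to −0.18 | 0.00 |
| Poor 3-month scorers, one arm only | 0.5 SD | −0.11 to −0.27 | 0.00 to 0.01 |
| Poor 12-month outcome, one arm only | 0 | −0.16 to −0.27 | −0.09 to −0.22 |

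Realised loss was 10% or 20% with no effect, and 15% or 27% with the 0.5 SD effect.

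**4. Other assumptions.** A logistic loss rule in one arm (log-odds 1.5 per SD of the 3-month score), 10% random loss in the other arm and about 20% lost in total gave completers-only bias of 0.09, 0.15, 0.19 and 0.21 SD for r of 0.4, 0.6, 0.7 and 0.8. A further set of assumed correlations and loss gave 0.08 to 0.18 SD for one-arm loss, and 0.04 to 0.05 SD for a common rule with a 0.5 SD effect. Using the early scores brought the bias to about zero in all of these.

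**5. Size against random error.** Root mean squared error = √(bias² + SD²), where SD is that of the estimate across trials.
- Largest gain in step 3 (one arm, effect 0.5 SD, r = 0.7, 20% target): √(0.265² + 0.402²) = 0.48 for completers, √(0.001² + 0.402²) = 0.40 for all visits.
- A case with no gain (common rule, effect 0.5 SD, r = 0.5, 10% target): √(0.050² + 0.374²) = 0.377 against √(0.003² + 0.382²) = 0.382.
- Random loss: the SD falls from 0.360 to 0.355 (r = 0.5, 10%) and from 0.385 to 0.370 (r = 0.7, 20%).

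**6. What it does to the next trial.** With n per arm ≈ 2(1.96 + 0.84)²/d² = 15.7/d², an effect of 0.5 SD needs about 63 per arm, 0.4 SD about 98 and 0.3 SD about 174. A shift of 0.1 to 0.2 SD in the input therefore matters, although random error in the same input is larger.

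**The case against.** The strongest objection is that exclusion is inferred. The article does not state a complete-case analysis and does not rule out imputation. Missing-data rules are commonly left to the full protocol or the SAP, neither of which is shown. That stands as far as it goes: a reader might infer that the plan discards these patients, and the text does not say so. But the single-time-point method is stated, and it gives the early scores no role in the primary comparison. The point addresses that choice.

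A reader might also infer bias whenever failing patients leave. Step 3 does not support this: the same rule in both arms with no true effect gave none. Nor does the article say that failing or re-operated patients stop follow-up; it plans to record complications and repeat surgery.

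A third tempting reading is that the early scores would repair the problem completely. They do so only when loss depends on scores already observed. Loosening and non-union may show after 3 months, and then much of the bias remains.

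Further limits stand. A baseline-adjusted comparison at one prespecified time point is an accepted analysis for a 30-patient pilot. The loss rates and correlations are assumed. The simulated estimator stands in for the full REML model, whose convergence and error rates in 30 patients were not tested. Finally, the abstract does compare scores at every follow-up, so the early scores are not unused altogether; but separate t-tests do not bring a patient without a 12-month score into the 12-month comparison.

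**Conclusion.** The point holds in conditional form, as a cheap improvement to a stated method. As worded, the primary analysis takes nothing from a patient lost after 3 months unless the 12-month score is imputed. The resulting bias is roughly 0.04 to 0.27 SD when loss follows the earlier scores and either differs by arm or a true effect exists (0.5 SD was assumed). It is nil under random loss, or under a common rule with no effect. These sizes rest on assumed correlations and on about 10 to 27% of patients lost; the article gives no figure for either.

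The standard error, about 0.32 to 0.41 SD, exceeds every one of these biases, so the gain is modest. For failures that arise after 3 months, 0.09 to 0.22 SD of an original 0.16 to 0.27 SD remains even with all visits used. A reader might further infer that the outcome SD passed to the next trial is distorted; no calculation here shows that, and it is not claimed.

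**What to change.** In Statistical methods, make the primary analysis one baseline-adjusted repeated-measures model fitted by REML to all available 6-week, 3-month and 12-month MOXFQ scores. Use arm-by-visit and baseline-by-visit terms, unstructured covariance and Kenward-Roger degrees of freedom. The arm difference at 12 months stays the primary contrast. Name the fallback covariance in advance, for example heterogeneous compound symmetry, for use if the model does not converge.

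Keep the 12-month-only comparison as a sensitivity analysis. Add a second one for failures arising after 3 months, for example by shifting the 12-month scores assumed for lost patients in the unfavourable direction over a stated range, separately by arm. Reword the abstract so that it names the same primary analysis and time point as Statistical methods. The secondary scores, which are to be analysed similarly, can follow the same model.

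The cost is wording only: no new visits or data. The trial was still recruiting when the article was written and the statistician is blinded to allocation, so the change can be made without knowledge of results. The downside is a slightly more complex model in 30 patients, with six covariance parameters for three visits.

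### The definitive trial is to be powered on the effect observed in a pilot of 15 per arm, which is too imprecise to serve as a planning target

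*Protocol article*

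**What the plan says.** The study has "two parallel treatment arms containing 15 participants each". The Methods/Design section states its aim: "The primary objective is to determine the range of improvement in outcome scores following these procedures". It adds that the primary and secondary objectives together (the latter being recruitment, dropout and acceptability) will feed a power calculation and the design of a larger trial. The abstract and the Ethics and dissemination section say much the same, referring to a range of scores or of changes.

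Under Patient recruitment, the article explains why this pilot has no sample size calculation: "There is no published data using the MOXFQ tool to assess differences between PPH and arthrodesis". It continues: "Therefore, a power calculation was not performed".

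The Statistical methods section is more specific. "The primary analysis will compare MOXFQ scores between the two treatment groups at 12 months using a" *t*-test adjusted for baseline. "Effect sizes will be presented as a point estimate, 95% confidence intervals and" *P* values. The section then closes with the planning rule: "The observed effect size will be used in a power calculation for a future definitive trial".

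**The concern.** The closing sentence follows directly on a between-group comparison and its effect estimates, so the effect size it refers to is most naturally the pilot's between-arm estimate on the MOXFQ at 12 months. The rule is unqualified. Nothing in the article names a difference worth detecting, limits the pilot's contribution to the SD, or provides for the estimate's uncertainty.

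A definitive trial's target difference should be one that would matter to patients and surgeons. A small pilot measures the between-arm difference much less reliably than it measures the SD. Required sample size varies with the inverse square of the target difference, so error in the estimate is magnified. A pilot that looks favourable by chance leads to an underpowered definitive trial. One that looks flat by chance leads to a trial far too large, or to none. Informing that trial is this study's declared purpose.

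**Working it through.** **Inputs from the article:** 15 per arm, 1:1 allocation, MOXFQ at 12 months adjusted for baseline, 95% confidence intervals. It gives no power, SD or target difference, so there is no figure of its own to reproduce.

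**Assumptions:** true standardised difference d of 0.3, 0.5 or 0.8; future trial at 80% power and two-sided alpha 0.05; no dropout; baseline to 12-month correlation r of 0 (unadjusted), 0.5 or 0.7.

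**Step 1. Precision of the pilot difference.**
- Unadjusted half-width: t(0.975, 28) × √(2/15) = 2.048 × 0.365 = 0.75 SD.
- Adjusted: t(0.975, 27) × √(2/15) × √(1 − r²), giving 0.65 SD at r = 0.5 and 0.54 SD at r = 0.7.
- With 13 per arm remaining, unadjusted: 0.81 SD.
- An observed d of 0.5 has a 95% CI (noncentral t) of −0.23 to 1.22. The n per arm is 63 at the point estimate and 11 at the upper limit. It is undefined across the interval as a whole, which includes zero.

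**Step 2. Sample size from the observed effect.** n per arm = 2(1.960 + 0.842)²/d² = 15.70/d². At the true effect this gives 175, 63 and 25 for d = 0.3, 0.5 and 0.8.

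**Step 3. When true power falls below 50%.** Power is about 50% at n = 2 × 1.960²/d² = 7.683/d². The planned n falls below that when the observed effect exceeds √(15.70/7.683) = 1.43 times the true one. Using the normal approximation with standard error √(2/15) = 0.365:
- d = 0.3: threshold 0.429; (0.429 − 0.3)/0.365 = 0.353, upper tail 36.2%. Adding 2.3% for large effects of the wrong sign gives 38.5%.
- d = 0.5: threshold 0.715; 0.215/0.365 = 0.589, tail 27.8%.
- d = 0.8: threshold 1.144; 0.344/0.365 = 0.942, tail 17.3%.

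**Step 4. Simulation, 400,000 pilots per setting, unadjusted.**

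| True d | n per arm needed | True power below 50% | Right sign, n more than double | Wrong sign | n within 0.8 to 1.25 times need |
|---|---|---|---|---|---|
| 0.3 | 175 | 39% | 20% | 21% | 7% |
| 0.5 | 63 | 28% | 26% | 8.5% | 12% |
| 0.8 | 25 | 17 to 20% | 24% | 1% | 20% |

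The spread at d = 0.8 comes only from how the small n is rounded. At d = 0.5 the 10th to 90th percentile of planned n is 16 to 1,146 per arm.

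**Step 5. Baseline adjustment in both trials, d = 0.5.** The standard error shrinks by √(1 − r²); the factor of 1.43 is unchanged.
- r = 0.5: 0.215/0.316 = 0.680, tail about 25%.
- r = 0.7: 0.215/0.261 = 0.824, tail about 20%.

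**Step 6. The alternative: fixed target, SD from the pilot.** n = 15.70 s²/δ², where s is the pilot SD, σ the true SD and δ the fixed target, taken here as equal to the true difference. True power falls below 50% only if s²/σ² < 7.683/15.70 = 0.489, that is, if a chi-square on 28 df is below 13.7. The probability is about 1%. At d = 0.5 the middle 95% of planned n is 35 to 100 per arm, with true power of 55% to 94%.

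**The case against.** The strongest defence is that the sentence should be read with the rest of the article. Methods/Design feeds the primary and secondary objectives into the power calculation, and dropout is one of them. A range of scores or changes could well supply an SD, and a standardised effect size already contains one. A reader might infer from the Statistical methods sentence that nothing else from the pilot will be used, or that a sample size is the only product. The article supports neither: dropout is an explicit input, and accrual and acceptability are named outputs. What remains is that the only sentence in the statistical section that names an input names the observed effect, and no other section retracts it or supplies a target difference.

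A second defence is that the analysis adjusts for baseline, so unadjusted figures overstate the imprecision. That is correct, and it reduces the problem without removing it (step 5). Any dropout works the other way.

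A third is that no comparative MOXFQ data exist. That explains why this pilot was not powered. A minimal important difference does not depend on a published comparison of these two operations.

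A reader might also count pilots with a reversed effect among the oversized trials, which at d = 0.5 raises that share from about 26% to 33%. Those pilots would hardly be planned as trials in the true direction, so they are left out. Nor does presenting *P* values amount to a planned efficacy claim. The article states none, and dropping them is a matter of preference.

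**Conclusion.** The concern holds for the one sentence in Statistical methods. Used as written, the rule gives an unreliable sample size. Across true effects of 0.3 to 0.8 SD, roughly one pilot in six to two in five would lead to a definitive trial with less than 50% true power. At d = 0.5 the share is 28% unadjusted and 20% to 25% with useful baseline adjustment, against about 1% with a fixed target and the pilot SD. These figures rest on an assumed true effect, correlation and future power, and on no dropout, but the direction is the same throughout the range examined.

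A reader might infer that the pilot itself is compromised. It is not: randomisation, data collection and the between-arm estimate are unaffected, and the SD, correlation and dropout rate can all be obtained from data already planned. The harm falls on the next trial. This should be fixed, but it is not a fatal fault.

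**What to change.** Replace the last sentence of Statistical methods with wording such as:

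> The definitive trial will be powered on a pre-specified minimal important difference in the primary MOXFQ score. The pilot will supply the SD of the 12-month score with its confidence interval, the correlation between baseline and 12 months, and the dropout rate. The calculation will allow for uncertainty in the SD, for example by using an upper confidence limit.

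Report the pilot's between-arm difference with its 95% confidence interval as descriptive, not as the planning target. The choice of confidence limit is open. With 28 degrees of freedom the 95% limits for the SD are about 0.79 and 1.35 times the estimate, and a one-sided 80% upper limit would be about 1.14 times. Dropout or a baseline covariate would change these slightly.

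The change needs no extra patients, visits or data. Its real costs are that a minimal important MOXFQ difference must be chosen and justified, since the article gives none, and that the definitive sample size may be somewhat larger because of the allowance for the SD.
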